## Abstract

**Introduction:**

With the aging of the population, knee osteoarthritis (KOA) is a common chronic osteoarthritic disorder among middle-aged and elderly people. Fu’s subcutaneous needling (FSN) and electroacupuncture (EA) are both effective means of treating KOA. FSN, with characterized by simple operation, quick effect, safety and green,is a modern acupuncture that integrates modern medicine with traditional acupuncture theory. Our team has demonstrated through clinical trials that FSN can effectively relieve pain and improve walking ability in patients with KOA. However, studies on the difference in clinical efficacy of FSN in treating KOA still lack clinical validation with large samples. The purpose of this study was to provide high-level clinical evidence for the clinical management of KOA by comparing the multicenter differences between FSN and EA in the treatment of this disease.

**Methods and analysis:**

This study is a prospective, multicenter, randomized controlled trial to compare the efficacy and safety of FSN with EA in the treatment of KOA. This study intends to recruit 300 patients with osteoarthritis of the knee in 6 tertiary hospitals in China, including Shandong Provincial Third Hospital, Shandong University, etc. The group was randomly divided into FSN group and EA group according to 1: 1 ratio. The intervention time is 30 min, and the treatment was carried out three times a week for 4 weeks, and the long-term follow-up was carried out one month after the treatment. The primary outcome index was the response rate of knee symptom relief, and the secondary outcome indexes were the numerical assessment of knee pain (NRS), WOMAC osteoarthritis index, quality of life evaluation (SF-12), 6-min walk test and safety evaluation.

**Clinical trial registration:**

ClinicalTrials.gov, ChiCTR2400080196.

## Highlights

Firstly, this is a multicenter, large-sample study. It will provide strong evidence for the efficacy and safety of FSN in the treatment of KOA.Secondly, we will conduct this trial in strict compliance with the protocol in order to realistically evaluate the efficacy.Thirdly, blinding is not possible for both operators and participants.Fourthly, patients recruited from various centers may differ in gender, age, and other disorders, so subgroup analyses may be necessary to determine the effectiveness of FSN in different subgroups.Fifthly, this study did not have a sham-Fu’s subcutaneous needling group to remove the placebo effect.

## Introduction

1

In a systematic analysis of the Global Burden of Disease Study, the number of KOA is predicted to increase by 74.9% (59.4–89.9) by 2050 compared to 2020 (1, 2). KOA is recognized as one of the 11th most disabling factors globally among 291 diseases (3). KOA, with degenerative changes of knee cartilage and secondary osteophytes, is a chronic osteoarthritic disorder (4). The main clinical manifestations are knee pain, localized tenderness with joint swelling, limited knee flexion and extension, and knee friction during activities. In severe cases, patients may suffer from the lack of mobility of the knee joint, which may lead to wasting muscle atrophy, and even symptoms such as knee inversion and knee valgus deformity (5). According statistics (6), the prevalence of KOA is 16%. It increases with age and seriously affects the quality of life of patients, placing a heavy burden on individuals, families and society (7). Therefore, early prevention and treatment are crucial for KOA patients.

The 2021 edition of the guidelines for osteoarthritis (8) points out that basic treatment methods including health education, functional exercise, and physical therapy are the preferred treatment modalities for patients. On this basis, topical NSAIDs (non-steroidal anti-inflammatory drugs) and oral NSAIDs are recommended as the first-line therapeutic drugs for KOA pain. Although medication can alleviate pain, it can be harmful to the human body, and patients may experience cardiovascular, gastrointestinal and other a series of adverse reactions (9). Surgery is expensive and traumatic, and many patients refuse it (10). These treatments are effective for KOA, but they have certain side effects, long treatment period and relatively high cost. Therefore, finding a safe and effective treatment for KOA with low recurrence rate and fewer side effects has become an urgent need for patients and doctors.

FSN is a needling activity that involves a sweeping maneuver in the subcutaneous tissue around or adjacent to the limbs of a confined ailment. FSN is, invented by [name] in 1996, a modern form of acupuncture that integrates modern basic medicine with traditional acupuncture theory (11). Compared with traditional acupuncture, FSN has distinctive characteristics due to its unique needles and needling method (Figure 1), and is effective in treating neck, shoulder, back, and limb pain due to a variety of causes (12, 13). FSN is to make the muscle as the therapeutic target, through sweeping and Reperfusion Approach (RA) eliminate the affected muscle, accelerate the circulation of local blood and lymphatic fluid, promote metabolism, so as to alleviate the muscle tension and spasm, thus restoring the muscle strength and coordination, increasing the mobility and stability of the joints, and promoting the rehabilitation of the knee joint function (14). There has been research evidence (11, 15, 16) that FSN can effectively improve pain and dysfunction in KOA, but there are few large sample studies comparing FSN with EA.

**Figure 1 fig1:**
[figure not shown]
Structure of the Fu’s subcutaneous needling needle. **(A)** ① Fu’s subcutaneous needling. ② Protective cover. ③ Soft tube. ④ Built-in rivets. ⑤ Buckle upwards. ⑥ Point-like bulge. ⑦ Stainless steel needle. ⑧ Slot. ⑨ Inserting device. **(B)** ① Pedestals. ② Inserting device turning lever. ③ Control button. ④ Fu’s subcutaneous needling.

The purpose of this study was to compare the difference in clinical efficacy between FSN and EA for the treatment of KOA, and to provide high-level clinical evidence for the clinical treatment of KOA. Thus, the clinical efficacy of FSN treatment for KOA patients will be evaluated, and the results of the study will provide a new reference for the clinical treatment of KOA.

## Methods and analysis

2

### The design of study

2.1

In this study, 300 patients with KOA will be recruited in six tertiary hospitals in China, including Shandong Provincial Third Hospital, Shandong University, from January 2024 to June 2026, and randomly divided into the FSN group and the EA group, with 150 cases in each group, to validate the clinical efficacy of the multicenter and large sample.

Subjects will receive either FSN or EA treatment. Both groups will be treated for 4 weeks, with 3 treatments per week and 1 treatment every other day, for a total of 12 times. The primary outcome measure is the response rate of knee symptom relief after 4 weeks of treatment (the proportion of patients with a decrease of ≥2 points on the NRS and a decrease of ≥6 points on the WOMAC at the end of 4 weeks of treatment compared with baseline). Secondary outcome indicators is the response rate of knee symptom relief, NRS, WOMAC scale score, 6-min walk test at 1, 2, 3, and 4 weeks of intervention and 4, 12, and 24 weeks after the end of intervention, as well as the Brief Quality of Life Scale (SF-12) score at 1, 4, and 4 weeks after the end of intervention. The flow chart of this experiment is shown in Figure 1.

The study and experimental procedures were approved by the Institutional Review Board. All subjects will be recruited from 6 centers in the country (Figure 2).

**Figure 2 fig2:**
[figure not shown]
Trial profile over 4 weeks.

## Participants

3

### Diagnostic standards

3.1

Referring to the diagnostic criteria for osteoarthritis of the knee in the Osteoarthritis Diagnostic and Treatment Guidelines (2018 Edition) formulated by the Joint Surgery Group of the Orthopedic Branch of the Chinese Medical Association (17).(1) Recurrent episodes of knee pain in the past month.(2) Age ≥50 years.(3) Joint stiffness in the morning not higher than 30 min.(4) Bone friction sound during knee joint movement.(5) X-ray (standing or weight-bearing position) showing narrowing of the joint space, sclerosis and/or cystic degeneration of the chondral bone, and formation of bone capillaries at the joint margins.

Knee Osteoarthritis can be diagnosed if 1 and any 2 of 2, 3, 4, 5 are met.

### Eligibility criteria

3.2

(1) Meets diagnostic criteria.(2) Age≤ 75 years old, regardless of gender.(3) Mean knee pain level NRS score ≥4 in the 2 weeks before enrollment.(4) Classification of the condition, KOA imaging classification (Kellgren Lawrence, KL) gradeIIto III.(5) Have not received acupuncture, herbal medicine, or other treatments in the last 1 month.(6) Agree to participate in this study and sign the informed consent form.(7) The above 6 items were met simultaneously to be included in the study.

### Inclusion criteria

3.3

(1) Combined with serious cardiovascular, cerebrovascular, digestive, respiratory, urinary, hematopoietic system and other diseases.(2) Knee pain caused by other diseases such as gouty arthritis, rheumatoid arthritis, and knee deformity.(3) History of surgery, joint cavity injection, or severe trauma to the target knee within the last 1 year.(4) Presence of contraindications to MRI examination, e.g., pacemakers, metal implants, fear of confined spaces, pregnancy preparation, pregnancy, etc.(5) Those who refuse to sign the informed consent form.

### Sample recruitment

3.4

In this study, 300 subjects will be recruited in 6 hospitals, namely Shandong Provincial Third Hospital, Shandong University, Tai’an Traditional Chinese Medicine Hospital, Guangdong Provincial Hospital of Traditional Chinese Medicine, Nanjing Hospital of Traditional Chinese Medicine, the Second Affiliated Hospital of Bengbu Medical College, and the First People’s Hospital of Wenling City, Zhejiang Province.

After eligible patients sign an informed consent form, statisticians will randomly assign subjects to either the treatment group or the control group according to block group randomization, with 150 subjects in each group. The control group will be treated with EA and the treatment group will be treated with FSN.

### Sample size calculation

3.5

This study is a randomized controlled trial design, the experimental group is the Fu’s subcutaneous needling group, the control group is the acupuncture group, the response rate of the research subjects is the main evaluation index of observation, according to the review of the literature/pre-experimental results, the response rate of the experimental group p1 is 0.56, and the response rate of the control group p2 is 0.45, set the bilaterally *α* = 0.05 that is, unilateral 0.025, the degree of certainty that is, the 1 - *β* is 0.9, and the sample size ratio of the experimental group to the control group is 1:1, the noninferiority threshold is-0.1. The ratio of the sample size of the test group to that of the control group is 1:1, and the non-inferiority cut-off value is-0.1. Referring to the method of Chow et al. (18), the sample size of the test group is 118 cases and the sample size of the control group is 118 cases by using the R language calculation. Considering 20% of lost visits as well as refusal of visits, at least 146 cases in the experimental group and 146 cases in the control group were eventually needed, totaling a sample size of 300 cases for inclusion.

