## Statistical analysis

7

Statistical analysis was performed by SPSS26.0 software, and all test data were expressed as mean and standard deviation.

A total of two types of independent variables were used in this study, namely the group independent variable (FSN group and EA group) and the time independent variable (pre-intervention, after 1, 2, 3, and 4 weeks of intervention, and after follow-up), in which the time independent variable was a replicated independent variable. Data were tested for normality using the Shapiro–Wilk test and Leven’s test for chi-square. If the data conformed to normal distribution, two-way repeated measures ANOVA (Two-Way Repeated ANOVA) was used to observe the Main Effect and Interaction of the two types of independent variables, i.e., time independent variable (within-group) and subgroup independent variable (between-groups), on the dependent variable, and when there was an Interaction between the two, a Boneferroni’s *post hoc* test (*Post Hoc*) was used. η^2^ was used for the expression of the effect size: η^2^ < 0.06 is a small effect size. 0.06 ≤ η^2^ < 0.14 is a medium effect size. η^2^ ≥ 0.14 is a large effect size. If the distribution did not conform to normal distribution, the Scheirer-Ray-Hare test was used and results were expressed as median and interquartile spacing.

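### Section 3.5 sizes the trial for non-inferiority, but no other section states that hypothesis; the 90% power does not carry over to showing a difference, where it is about 40 to 48%

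*Protocol article*

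**What the plan says.** Section 3.5 (Sample size calculation) takes the response rate as the main index. It assumes that "the response rate of the experimental group p1 is 0.56" and that "the response rate of the control group p2 is 0.45". The error rate is two-sided 0.05, "that is, unilateral 0.025", power is 0.9 and allocation is 1:1. It then says that "the noninferiority threshold is-0.1", and the next sentence gives the same cut-off again. The result is 118 per arm, raised for 20% loss and rounded to 300 in total, which Section 2.1 splits as 150 per arm.

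The aim is put differently elsewhere. The Introduction says: "The purpose of this study was to compare the difference in clinical efficacy between FSN and EA for the treatment of KOA". The abstract likewise speaks of comparing FSN with EA. Sections 2.1 and 6.1 define the primary outcome as the proportion of responders after 4 weeks, with no hypothesis attached. Section 7 (Statistical analysis) says that "two-way repeated measures ANOVA (Two-Way Repeated ANOVA) was used to observe the Main Effect and Interaction" of group and time, with a rank-based alternative for non-normal data. It mentions no margin, no confidence-interval rule and no method for comparing two proportions.

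**The concern.** The hypothesis that sizes the trial and the question the trial says it asks are not visibly the same. Two things follow.

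First, a reader who takes the stated purpose at face value will attach the 90% to finding a difference between the treatments. It does not belong there.

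Second, the document does not settle what counts as success. Suppose the 95% confidence interval for FSN minus EA ran from -5 to +19 percentage points. Against the margin in Section 3.5 that is a positive trial. Against the purpose in the Introduction it is a failure to show a difference. Unless one reading is fixed beforehand, the choice can be made after the data are seen.

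**Working it through.** **Inputs (all from Section 3.5 unless noted).** FSN rate 0.56; EA rate 0.45; assumed difference 0.11; margin 0.10; one-sided 0.025 (z = 1.960); power 0.90 (z = 1.282); 1:1 allocation; 20% loss. Randomised number 150 per arm (Section 2.1), so about 150 × 0.8 = 120 per arm evaluable.

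**1. Reproduce the plan's figure.**

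- Variance term: 0.56 × 0.44 + 0.45 × 0.55 = 0.2464 + 0.2475 = 0.4939.
- n per arm = (1.960 + 1.282)² × 0.4939 / (0.11 + 0.10)² = 117.7, so 118. This matches exactly.
- The distance that carries the 90% is 0.21: the assumed 11-point benefit plus the 10-point margin.
- Non-inferiority power under these rates is 90.1% at 118 per arm, 90.5% at 120 and 95.5% at 150.

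**2. Same inputs, showing a difference.** The margin drops out and the distance falls from 0.21 to 0.11.

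- n per arm for 90% = (1.960 + 1.282)² × 0.4939 / 0.11² = 428.9, so 429 (433 with the pooled variance). Allowing for 20% loss, 433 / 0.8 gives 542 per arm, or 1,084 in total.
- Power = Φ(0.11 / √(0.4939 / n) − 1.960). At 118: √(0.4939 / 118) = 0.0647, and Φ(1.700 − 1.960) = 0.398.

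| Evaluable per arm | Unpooled | Pooled | Exact (chi-square test) |
|---|---|---|---|
| 118 | 39.8% | 39.3% | 38.1% |
| 120 | 40.3% | 39.8% | 38.5% |
| 150 | 48.3% | 47.8% | 50.1% |

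**3. Sensitivity: non-inferiority if the arms are equal.** With both rates at 0.45, power = Φ(0.10 / √(2 × 0.45 × 0.55 / n) − 1.960), which is 33.9% at 118 per arm and 41.3% at 150. At 118 per arm, common rates from 0.45 to 0.56 give 33.6% to 34.0%.

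**4. Is the example interval realistic?** The 95% half-width under the planned rates is 1.960 × 0.0647 = 12.7 points at 118 per arm, and 1.960 × √(0.4939 / 150) = 11.2 points at 150. The interval from -5 to +19 has a half-width of 12 points, so it is the kind of result this trial could produce.

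**The case against.** The best defence is that Section 3.5 already supplies everything a non-inferiority hypothesis needs: endpoint, margin, one-sided level, power and assumed rates. No section uses the word superiority. Comparing a difference is generic language, and a non-inferiority trial also estimates a difference. A formal confidence-interval rule is often left to an analysis plan, which is not shown here. Assuming a benefit when sizing a non-inferiority trial is permissible, and the article attributes the two rates to literature or pilot results that cannot be inspected.

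Much of this stands, and it rules out several stronger readings that a reader might infer:

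- **That Section 7 commits the primary endpoint to a test of difference.** It does not. Repeated-measures ANOVA and its rank-based alternative suit the repeated scores; no test is named for the binary responder rate. Section 7 shows only that no non-inferiority analysis is present.
- **That this is a declared superiority trial with 40% power.** No superiority hypothesis is stated. The 40% applies if the stated purpose is read as showing a difference.
- **That a non-significant difference would be uninterpretable.** It would be inconclusive about superiority, but the interval could still be read against the stated margin.
- **That the power under equal efficacy exposes an error.** It is a sensitivity figure. Whether 11 points is optimistic cannot be judged from the article.

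What the defence does not remove is the inconsistency inside the document. The primary hypothesis belongs with the objective, and here it can only be inferred from the sample size paragraph.

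**Conclusion.** The point holds as an inconsistency between the sizing hypothesis and the stated aim, not as an arithmetic error: the 118 is right for the calculation that was made. The 90% is valid only for non-inferiority at a margin of -0.10 with FSN truly 11 points better. For showing a difference, the article's own inputs give about 40% at the 118 to 120 per arm expected to be evaluable, and about 48% if nobody is lost (50% by exact enumeration). These figures rest on the rates of 0.56 and 0.45, two-sided 0.05, and a simple comparison of two proportions without adjustment for centre. The matter should be settled before results are known, because it decides what the trial may conclude.

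**What to change.** 1. In the abstract and Sections 1, 2.1 and 3.5, state that the primary hypothesis is non-inferiority of FSN to EA on the week-4 response rate, with a margin of -10 percentage points.
2. In Section 7, make the primary analysis the two-sided 95% confidence interval for the difference in response rates (FSN minus EA). Conclude non-inferiority if the lower limit is above -0.10. Test superiority only after that, in fixed sequence, which costs no alpha.
3. In Section 3.5, say that the 90% is for non-inferiority assuming an 11-point benefit, and that power for superiority is about 40 to 48%. The non-inferiority power if the arms are equal (about 34% at 118 per arm, 41% at 150) may be added as a sensitivity figure.
4. If showing a difference is the real aim, remove the margin and replace the 90% with 40 to 48%.

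The cost is wording and a less favourable stated power. The 300 patients stay as planned under either route; only a wish to keep 90% power for a difference would require a larger trial.

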## Randomization and blinding

4

Researchers will screen patients for eligibility and recruiters will be responsible for recruiting 300 individuals. Random numbers generated using Stata V.14.0 will be packaged and hidden in envelopes by a third-party statistician according to the principles of block randomization.

Due to the physical specificity of FSN treatment and EA treatment, it was not possible to blind participants and subjects. However, the researchers responsible for data collection from participants and statistical analysis will be unaware of the allocation in order to minimize bias in the reporting of subjective results.

## Intervention methods

5

### Electroacupuncture group

5.1

Disposable Warren brand sterile acupuncture needles of 0.30mmx25mm or 0.30mmx40mm length were used, depending on the depth of the acupuncture point. EA treatment points (Table 1; Figure 3) will be referred to the study published by [name] in 2021 (19), including 5 necessary points, Du Bi (ST35), Nei Xi-Yan (EX), Qu Quan (LR8), Xi Yang-Guan (GB33), and A Shi point; According to different meridian diseases, 3 optional acupoints were selected, Foot Yangming meridian: Fu Tu (ST32), Liang Qiu (ST34), Zu San-Li (ST36), Feng Long (ST40), He Ding (EX); Foot Taiyin Spleen meridian: Xue Hai (SP10), Yin Gu (KI10), Yin Ling-Quan (SP9), San Yin-Jiao (SP6), Tai Xi (KI3), etc.;Foot ShaoYang Gallbladder meridian: Feng Shi (GB31), Yang Ling-Quan (GB34), Wai Qiu (GB36), Xuan Zhong (GB39), Zu Lin-Qi (GB41), etc.; Foot Solar Urinary Bladder meridian: Wei Yang (BL39), Wei Zhong (BL40), Cheng Shan (BL57), Kun Lun (BL60), etc. One group of EA was connected to Qu Quan/Xi Yang-Guan, and another group of EA was connected to the other two optional acupoints, with a frequency of 1 HZ, wave type of continuous wave, and current intensity to the extent that slight contraction of the muscles occurred; each treatment will last for 30 min, and the treatment will was performed 3 times per week, once every other day, for a total of 12 treatments in 4 weeks.

**Table 1 tab1:** EA treatment points.

Acupoint	Acupoint number	Acupoint position
Necessary Acupoints		
Du Bi	ST35	In the anterior knee region, in the lateral depression of the patellar ligament
Nei Xi-Yan	EX	At the knee, in the center of the medial depression of the patellar ligament
Qu Quan	LR8	In the knee, at the inner end of the popliteal crease, in the concave inner edge of the semitendinosus tendon
Xi Yang-Guan	GB33	In the depression between the knee, the posterior upper edge of the lateral epicondyle of the femur, and the tendon of the biceps femoris muscle and the iliotibial tract
A Shi point		Pain is the acupoint, and if there is pain, it is the acupoint
Optional Acupoints		
Fu Tu	ST32	At the anterior femoral region, six inches above the patellar floor, at the line connecting the anterior superior iliac spine and the lateral end of the patellar floor.
Liang Qiu	ST34	In the anterior femoral area, 2 inches above the patellar floor, between the lateral femoral muscle and the tendon of the rectus femoris muscle
Zu San-Li	ST36	On the outer side of the calf, 3 inches below the calf’s nose, 1 transverse finger outside the anterior tibial spine
Feng Long	ST40	On the outer side of the calf, 8 inches above the tip of the outer ankle, at the outer edge of the anterior tibial muscle, at a transverse finger on the outer side of the Tiaokou
He Ding	EX	In the anterior knee region, in the depression above the midpoint of the patellar floor
Xue Hai	SP10	In the anterior femoral area, 2 inches above the medial end of the patella, at the bulging point of the medial femoral muscle
Yin Ling-Quan	SP9	In the depression between the medial condylar edge of the tibia and the medial edge of the tibia on the inner side of the calf
Yin Gu	KI10	Posterior to the knee, on the transverse popliteal stripe, lateral margin of the semitendinosus tendon
San Yin-Jiao	SP6	On the inner side of the calf, 3 inches above the tip of the inner ankle, at the posterior edge of the medial edge of the tibia
Tai Xi	KI3	In the ankle area, the depression between the inner ankle tip and the Achilles’tendon
Feng Shi	GB31	In the femur, 7 inches above the patellar floor: with the hand upright and the palm pressed against the thigh, the depression indicated by the middle finger tip and the posterior edge of the iliotibial tract
Yang Ling-Quan	GB34	On the outer side of the calf, in the depression below the anterior part of the fibular head
Wai Qiu	GB36	On the outer side of the calf, 7 inches above the outer ankle tip, at the anterior edge of the fibula
Xuan Zhong	GB39	On the outer side of the calf, 3 inches above the outer ankle tip, at the anterior edge of the fibula
Zu Lin-Qi	GB41	On the dorsum of the foot, in front of the junction of the 4th and 5th metatarsal bones, in the lateral depression of the extensor digitorum longus tendon of the 5th toe
Wei Yang	BL39	At the knee, along the popliteal crease, at the inner edge of the biceps femoris tendon
Wei Zhong	BL40	In the posterior knee area, at the midpoint of the popliteal crease
Cheng Shan	BL57	At the intersection of the gastrocnemius abdomens and tendons in the posterior region of the calf
Kun Lun	BL60	In the depression between the outer ankle tip and the Achilles tendon in the ankle area

